### Trial objective and hypothesis

The current study will investigate the effectiveness of a newly developed internet-based ABM (iABM) training as an add-on intervention to treatment as usual (TAU; consisting of protocolled CBT-based interventions), in alcohol and cannabis dependent outpatients. More specifically, the study will evaluate whether this new iABM training enhances treatment outcomes, and may be a cost-effective component that should be added to treatment in addiction care. The focus of the study is to examine the additional effects of iABM training on changes in substance use, craving, and relapse rates. Measurements of attentional bias will serve as a manipulation check for the efficacy of the current training to successfully modify attentional bias. This is important because only if the current iABM intervention is effective in modifying patients’ attentional bias it can be expected to have an impact on their substance use.

Based on this objective, we will test the hypothesis that patients who receive iABM intervention, compared to controls, will show less substance use, less craving, and lower relapse rates at post-measurement and 6 and 12 months after treatment. In addition, we will test if patients who received iABM intervention will show increased health and reduced physical and psychological complaints. Furthermore, we predict that these patients will show a reduction in health care usage 6 and 12 months after the intervention. Moreover, we predict that the effects on the individual and societal level will cause a decrease in societal costs that outweighs the additional costs of iABM intervention. Finally, we hypothesize that participants who show a stronger attentional bias and higher rates of craving before starting the ABM training will benefit most from this intervention.

## Methods and design

### Trial design

The present study is a multicentre randomized controlled two-armed, parallel-designed trial with one treatment arm (iABM intervention) and a control arm, which will be divided into a placebo condition and a TAU-only condition (see Fig. 1). The inclusion of these two control conditions enables (1) the investigation of the effect of TAU + iABM intervention, related to TAU-only, and (2) the control for a possible placebo effect, by comparing the iABM condition with the placebo condition. The design of the study enables that iABM intervention, as well as the placebo condition, can be provided parallel to treatment as usual (TAU). Recruitment will take place in four addiction care centres in the Netherlands (*Iriszorg*, *Novadic-Kentron, Tactus Verslavingszorg and Verslavingszorg Noord Nederland*). There are two treatment intensities in the Dutch mental health care system. All participants who will be included in this study will receive the lower dose treatment, in which TAU consists of 350 to 750 min of protocolled CBT-based intervention in a specialized addiction care institution, including a 30% range of possible additional interventions, such as medication. Whether therapists make use of such additional intervention components depends on the severity of addiction and possible related problems of the patients. Patients who are ascribed to this intensity of treatment are expected to live relatively independent and to report less comorbidity. The additional effects of the iABM intervention will be tested directly after the end of TAU, which is also the end of the training, and 6 and 12 months later. For an overview of the planned timeline of the study, see Fig. 2.

**Fig. 1 Fig1:**
[figure not shown]
Participant flowchart

**Fig. 2 Fig2:**
[figure not shown]
Expected timeline of completion and reporting of results

This study was approved by the ethical committee of the University Medical Centre of Groningen (UMCG; METc 2016/026) and is registered at the Netherlands Trial Register (NTR5497). It is partially funded by ZonMw (The Netherlands Organisation for Health Research and Development; 80–84,300–98-61,035), and co-financed by Verslavingszorg Noord Nederland. Modifications to the study protocol will be communicated with the ethical committee as well as with ZonMw. This trial protocol is written in adherence with the Standard Protocol Items:

Recommendations for Interventional Trials (SPIRIT) guidelines.

### Participants and procedure

Participants will be treatment-seeking adult patients diagnosed with alcohol use disorder (AUD) or cannabis use disorder (CUD) with an indication for TAU in addiction care as described above. Recruitment will take place at the four addiction care centres. The therapists will inform all their patients during the intake or the first session of TAU about the possibility of participating in a study. Interested patients will receive a folder, containing a leaflet from the Dutch government about scientific research in general, a patient information letter with specific information about the current study, an informed consent form with envelope, and a small card with contact information of the studies’ helpdesk. If patients give permission to their therapist, he/she will forward the patients’ contact information to a researcher, who will call them a few days later in order to screen for eligibility and to give a brief oral explanation about the study rationale and the norms of data processing. Thus, recruitment will be done by the researchers, while the therapists are responsible for providing the first information to their patients. Patients will be included if they (a) are 18 years or older, (b) have a main diagnosis of AUD or CUD, and (c) have an indication for TAU in addiction care as described above. A contra-indication for participation is (a) a problem with compulsive gaming, gambling disorder, or internet addiction as measured with a short version of the C-VAT 2.0 [42] and/or (b) the absence of a personal computer or laptop and/or no access to internet. Eligible patients who decide to participate will be asked to sign the informed consent form and to send it to the researcher. After receiving the signed informed consent form, they will be assigned to the online registration and monitoring tool of the study. The signed informed consent form needs to arrive at the researchers’ office within the period of the first three sessions of TAU. Otherwise the potential participant is excluded from the study, as early effects of TAU could distort pre-measures too much.

After assignment to the system, all participants will be invited by e-mail to complete the baseline assessment. Participants who are assigned to the TAU-only condition will thereafter receive TAU. Participants who are assigned to one of the trainings (active or placebo) will thereafter read the training instructions. Furthermore, they can watch an animated video in which the training is explained. Hereafter a short 5-min practice session of the training follows. One day after completing the baseline assessment and the practice session of the training, participants in one of the training conditions will receive an invitation for the first training session by e-mail. The following three weeks, participants will be asked to train on a daily basis. Thereafter, the number of training sessions per week will decline. Participants will train three times a week for another three weeks and finally once a week until the end of TAU. Thus, the actual number of training sessions is dependent on the duration of TAU. The lower doses treatment in the Dutch addiction care usually takes 3 to 6 months, depending on the severity and the progress of the patient. During the whole training period a researcher will monitor the process of the patients and whether they train regularly. After three training sessions are missed, patients will receive an automatic reminder by e-mail. If this does not result in the continuation of the training the researcher will contact the patient via the preferred way (phone, e-mail, text message or app) in order to ask whether there are any problems or doubts about the participation in the study.

An important part of the study is the involvement of the therapists. In order to improve adherence, the researchers will train the therapists before the inclusion of participants starts. The training will consist of the following parts (1) general background knowledge about attentional bias and ABM, (2) design and important parts of the study, and (3) the role of the therapists. During the training all therapists will receive a protocol in which all important aspects are described. In the first session of TAU after patients are assigned to the study, therapists will identify the time of the day patients’ craving is strongest and will instruct the patient to complete the ABM task at this particular time of the day. Furthermore, during each following treatment session of TAU, the therapist will ask the participant whether he/she trains on a regular basis, and will engage in motivational counselling if this is not the case.

During the last week of TAU in addiction care, participants in the training conditions will receive the last training invitation by e-mail. After completion, they will be invited for the post-assessment. Participants in the TAU-only condition will also receive the invitation for the post-assessment in their last week of TAU. Finally, 6 and 12 months after the end of TAU, all participants will receive an invitation for the follow-up measurements by e-mail. In case a participant does not respond to these invitations, the researcher will remind the patient via the preferred way (phone, e-mail, text message or app). Throughout the length of the whole project, a sounding board group will meet four times to monitor the process of the study. The group will include a researcher, a therapist, and a member of the client council of each addiction care centre, and an implementation professional.

To enhance the motivation of participants to train regularly and to make the training more appealing, some game-like features were added to the original version of the BITT. First, the training consists of 12 different levels, gradually increasing in difficulty. The construction of the levels is based on three factors: Moving speed of squares, interval of switching of images within squares, and interval of switching of images between squares. In order to adapt the difficulty of the levels to the abilities of the current population, the speed of the levels was tested in a small group of patients diagnosed with AUD and CUD in one of the addiction care centres during the test phase. In the beginning of the training phase, all participants start with level one and thereafter can unlock more challenging levels by reaching a certain amount of points. This cut-off score is 80, which equals a tracking time of 2 min per block. The high-scores of each level are stored, so that participants can challenge themselves by reaching higher scores during the next block or training session. Participants are instructed to choose a level that is challenging, but not too difficult and thereby frustrating. The number of trials depends on the level at which participants are training. Second, participants receive feedback about their performance in the form of points, calculated for each block. The more accurately participants track the substance-irrelevant image with the mouse cursor, the higher their score. While training, the participants’ accruing score is indicated by the length of a green bar shown on the screen. A mark on the bar gives them feedback about whether they already unlocked the next level. Next to the bar, they can also see the remaining time per block. There are two versions of the BITT: One contains stimuli that are relevant for patients diagnosed with AUD, whereas the other contains stimuli relevant for CUD patients.

To test the effect of the BITT on participants’ ability to engage attention with substance-irrelevant cues while ignoring substance-relevant cues, we will test the increase in tracking time of the substance-irrelevant cue over the course of treatment. To test the effect of the BITT on participants’ ability to disengage attention from the currently attended locus whenever substance-relevant cues appear there, we will examine the change in switching time over the course of treatment. To measure transfer of the improvement in BITT performance in terms of enhanced orientation towards substance-irrelevant cues and enhanced ability to disengage from substance cues, we also included a visual search task to measure attentional bias (see below).

#### Placebo condition

The placebo condition is designed to be similar to the active BITT, and the stimuli, the design/layout, the temporal parameters, and the construction of levels are all equal to the active intervention. However, in the control condition the task is not configured to reduce attention to substance-related cues.

In contrast to the active intervention, the placebo condition consists of four substance-relevant and four substance-irrelevant images moving on the screen. Participants are instructed to equally pay attention to all eight images until one of the squares turns green. They are asked to click on this green-filtered image as quickly as possible. The green filter appears in an unpredictable location at unpredictable time intervals. Throughout the task, the squares containing substance-relevant and substance-irrelevant images turn green equally often (50:50 ratio).

#### Task stimuli

The stimuli of the alcohol and cannabis version of the BITT and the placebo condition consist of the same two sets of 64 images (500 × 500 pixels). Whereas the first set of 64 images is used during most of the training sessions, the second set is only used for the last training session in order to measure generalization to new (untrained) stimuli. The 32 substance-relevant images of the alcohol version show different alcohol beverages, such as beer, wine, or whiskey. The substance-irrelevant category consists of 32 non-alcoholic drink images (e.g., soda, tea, or coffee). The images of both categories show a bottle, a bottle with an empty glass, or a bottle with a filled glass. The cannabis version is constructed of 32 substance-relevant images showing objects related to cannabis use (e.g., weed, joint, or rolling paper) and 32 substance-irrelevant pictures containing office products (e.g., pen, post-it, or paperclips). All used pictures were used in earlier studies [11, 43]. For each block of a training session, 8 substance-relevant and 8 substance-irrelevant images are randomly drawn from the 64 available images. For the next block, 16 other pictures will be used. Thus, throughout each training session all 64 images are presented to the participant. As images switch within an unpredictable time interval and dependent on the actual level, the number of times an image is presented within one block is not fixed. Yet, as participants reach higher levels and the speed of switching increases, each image is presented more often within one block. The background of all images is white and they are matched by colour, type of bottle/package, and size of bottle/package. Furthermore, all stimuli are passive, which means that no persons are shown in the pictures. For an example of training stimuli, see Fig. 3.

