### Baseline, post measurement and follow-ups

#### Attentional bias assessment

Attentional bias to substance-related cues is measured using the *Odd One Out Search Task* approach (originally introduced by [44]], and later modified by other researchers). In this task, participants have to identify whether 20 pictures (500 × 500 pixel), presented in a 4 × 5 matrix, all belong to the same single category or whether one picture belongs to a category distinct from all the others. Dependent on the diagnosis of the participant, all pictures belong to one of the following three categories: alcoholic drinks, non-alcoholic drinks, and flowerpots or cannabis-related objects, neutral daily life devices, and flowers, respectively for AUD and CUD. Due to these three categories, there are three conditions in which no *odd one out* picture can be found in the matrix (e.g., all 20 pictures show alcoholic drinks). Accordingly, there are six possible combinations in which an *odd one out* picture is present (e.g., 19 pictures contain cannabis-related objects and one picture shows a flower). For an overview of all nine conditions per diagnoses see Table 1. The possible combinations of conditions are balanced and the order of trials is random. The task is divided into three blocks of 24 trials each, and within each block, there will be 18 trials with an *odd one out* picture and 6 trials without an *odd one out* picture. The duration of each trial is dependent on the reaction time of the participant, but last 10 s at most. Responses are given by the answer buttons on the keyboard; 1 for ‘yes, there is an *odd one out*’ and 0 for ‘no, there is no *odd one out*’. Between trials, participants are instructed to focus their attention on a red fixation cross in the middle of the screen, which is presented for 500 ms. For both versions (alcohol and cannabis), we will use a total of 90 pictures, meaning that there are 30 different pictures per category. Per trial, the 20 pictures that are presented in the matrix are randomly drawn from the available pictures. The pictures of the alcoholic and non-alcoholic drinks [43] and the pictures of cannabis-related objects and neutral daily life devices [45–48] were used in earlier studies and permission was asked. The pictures of flowerpots and flowers were taken for the purpose of the current study.

**Table 1 Tab1:** Type and amount of trials in the Odd one out task, separated for AUD and CUD

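### New pictures appear only in the last training session, always as the same set, so the within-task generalisation result is confounded with picture-set difficulty

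*Protocol article*

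**What the plan says.** The section Task stimuli states that "the BITT and the placebo condition consist of the same two sets of 64 images", for both the alcohol and the cannabis version. It assigns the sets by session: "the first set of 64 images is used during most of the training sessions", while "the second set is only used for the last training session in order to measure generalization to new (untrained) stimuli". Each block uses 16 pictures and a session has four blocks, so "throughout each training session all 64 images are presented to the participant". On comparability, the section gives the pictures a white background and adds that "they are matched by colour, type of bottle/package, and size of bottle/package".

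The section Attentional bias modification training names two within-task measures. For engagement, "we will test the increase in tracking time of the substance-irrelevant cue over the course of treatment". For disengagement, "we will examine the change in switching time over the course of treatment". Neither statement says whether the last session, with its different pictures, belongs to that course. The same section adds the Odd One Out visual search task as a measure of transfer.

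The section Placebo condition describes a different response: participants click an image when it turns green. They do not follow a substance-irrelevant image.

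**The concern.** The last session has a stated purpose, to measure generalisation to untrained stimuli, and the layout cannot deliver it cleanly. As described, every participant meets set 2 once, in the final session and in all four blocks. There is no set 2 performance from before training, no set 1 performance in that same session, and no exchange of sets between participants. A change in performance at the last session could come from novelty, from set 2 being easier or harder to tell apart, or from something particular to that session, and the data cannot say which.

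The Background argues that multiple sessions are probably needed for the effect to carry over to novel stimuli, so the session tests part of the rationale for the training. Picture allocation is fixed when the software runs, so an analysis plan written later cannot recover the missing contrast.

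**Working it through.** The protocol gives no figure for this point to reproduce, and the sample size is not an input.

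**Inputs**
- Schedule (Participants and procedure): daily for 3 weeks, three times a week for 3 weeks, then weekly to the end of TAU, which usually lasts 3 to 6 months. I take this as 13 to 26 weeks with every session done.
- Session: 4 blocks of 2.5 min, 16 pictures per block (Attentional bias modification training; Task stimuli).
- Scoring: 80 points correspond to 2 min of tracking in a block.
- Assumed, not in the protocol: a set difference of up to 5 points in either direction.

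**1. Number of sessions.** 3 × 7 + 3 × 3 = 30, plus 13 − 6 = 7 or 26 − 6 = 20 weekly sessions, gives 37 to 50. Only the final one uses set 2. Since 4 × 16 = 64, 0 of its 4 blocks show trained pictures.

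**2. Aliasing.** Write last-session performance as the extrapolated practice trend + N (novelty) + D (set 2 minus set 1 difficulty) + L (effect specific to the last session). N, D and L share one indicator, so only N + D + L can be estimated. The rank of the session-level design matrix confirms this, with the same result for 37 and 50 sessions:
- As planned, with intercept, linear and log session trend, novelty and set: 5 columns, rank 4.
- As planned, adding a last-session effect: 6 columns, rank 4.
- Sets swapped between participants: 5 columns, rank 5. Adding a last-session effect: 6 columns, rank 5.
- Sets swapped, and trained and untrained blocks mixed in the last session: 6 columns, rank 6.

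A smooth practice trend can be extrapolated from the earlier sessions, so ordinary session effects are not the obstacle. N and D stay aliased in any model of the planned design.

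**3. Size of the bias.** 80 points = 120 s, so 1 point = 1.5 s, a full block of 150 s is 100 points, and 5 points = 7.5 s. Suppose the true effect of novelty is a loss of 5 points and L = 0. The apparent loss is 5 − 5 = 0 if set 2 is 5 points easier, 5 if the sets are equal, and 5 + 5 = 10 if set 2 is 5 points harder.

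**4. Training curve.** If a straight line is fitted by least squares over S sessions, a shift d in the last session changes the estimated total gain by 6d(S − 1) / [S(S + 1)]. With d = 5:
- S = 37: 30 × 36 / (37 × 38) = 1080 / 1406 = 0.77 points.
- S = 50: 30 × 49 / (50 × 51) = 1470 / 2550 = 0.58 points.

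Against calendar day, where the late weekly sessions carry more leverage, the change is 0.8 to 1.4 points. Overall this is 12% to 28% of the shift.

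**5. Why the repaired design works.** In the last session, the untrained-minus-trained difference is N + D for participants trained on set 1 and N − D for those trained on set 2. L cancels within the session, and the average over equal halves is [(N + D) + (N − D)] / 2 = N.

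**The case against.** Several counter-arguments have force.

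- **No such contrast is defined.** The protocol says only that the last session measures generalisation. The Clinical analysis section contains no analysis of training-task performance, and the choice of comparison may be left to an analysis plan. One candidate is the last session against the first, when set 1 was also new. That compares new with new, but it still needs the two sets to be equally difficult, so it does not remove the confounding.
- **The pictures are matched.** This makes a large set difference less likely. The text does not say that the matching was done between set 1 and set 2, nor that difficulty was compared. The pilot that is described tested the speed of the levels.
- **A condensed article may omit counterbalancing.** This is possible, but the text assigns the first set and the second set to fixed sessions and describes no exchange.
- **Generalisation within the task is not an outcome.** It is neither primary nor secondary. The declared manipulation check is attentional bias, and the Odd One Out task carries the between-arm test. This stands and limits the importance of the point.

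Three stronger readings are tempting and not supported. A reader might infer that set difficulty decides the result whatever was learned. It biases the result by the set difference, and would have to match the whole training gain to decide it; no figure suggests that. A reader might infer that the training-effect estimate is spoiled. The effect is a fraction of the shift and is avoidable in the analysis. A reader might also infer, because the drink pictures of both tasks cite a common source, that the Odd One Out task reuses trained pictures. A shared source does not show shared pictures, the cannabis pictures cite different sources in the two tasks, and active and placebo participants see the same training pictures.

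**Conclusion.** The point holds with a narrow scope. As described, novelty, picture set and last-session effects cannot be separated, and any difference in set difficulty biases the within-task generalisation result by exactly that amount. The size of the difference is unknown; 5 points is only an illustration. The placebo arm cannot supply the correction, because its task produces neither of the two measures.

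The training trend is affected slightly, and only if the last session is included in it. Substance use, craving, relapse and the between-arm Odd One Out comparison do not depend on the picture sets. The conclusion assumes that the sets were not exchanged between participants and were not shown to be equally difficult; evidence of either would weaken it.

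**What to change.** Before recruitment:
- Swap the sets between participants, so that half train on each, balanced within condition and addiction type.
- In the last session, run two blocks of trained and two of untrained pictures (2 × 16 = 32 pictures of each kind), in random order and at one level. Estimate generalisation as the within-session untrained-minus-trained difference.
- Fit the trends in tracking and switching time on trained-picture blocks only.

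This changes the picture lists in the software and adds no patient, session or training time. The costs are two untrained blocks per participant instead of four, and the loss of the self-chosen level within that one session.

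If recruitment has already started, end the training trend at the last set 1 session, and report the last-session result as exploratory and confounded with picture set.
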